### 2.7. Statistics

Significance is set at an alpha value of 0.05. SAS (Cary, NC) software will be used for statistical analysis. All efficacy analyses will be performed in the intent-to-treat population, defined as all patients who are randomized. Subset analyses will be performed by habitual marijuana use. 

The primary endpoint is the change in morphine equivalents and will be assessed as: post-randomization (48 h after randomization) minus pre-randomization (24 h prior to randomization). No imputation will occur for the primary endpoint. The change in morphine equivalents (mg) will be analyzed with an analysis of covariance (ANCOVA) model to examine the effect of treatment arm, adjusted for age, gender, injury severity score, and clinical characteristics that differ between groups with *p* < 0.15. Of note, our study inclusion criteria allow for patients to present with polytrauma. We anticipate the majority of patients will have injuries to the thorax and extremities, with few patients presenting with severe TBI because administration of opioids and other drugs that alter a neurological assessment tend to be used sparingly. Should there be differences in injury patterns, despite the 1:1 randomization procedure, these differences will be adjusted for in the primary ANCOVA analysis.

Secondary efficacy analyses include the difference between treatment groups in: hospital disposition, hospital complications, and analgesic complications, reported as proportion (%) and analyzed with chi-square tests; morphine equivalents over the hospitalization, hospital length of stay (days), time (h) to transition to non-opioid analgesia, pain NRS scores at all specified time points, reported as median (IQR) and analyzed with a Wilcoxon rank-sum test. Analgesic complications will be described by severity as mild, moderate and severe.

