### 2.8. Sample Size

The planned enrollment is 122 patients total randomized 1:1 across two study arms: dronabinol or no dronabinol (systemic analgesia only). The sample size is based on a 38% reduction in morphine equivalents with adjunctive dronabinol vs. an 8% reduction in morphine equivalents for systemic analgesics only, with a pooled standard deviation of 58. The analysis was performed using two sample mean tests with normal approximation and equal weights. These estimates were derived via bootstrapping of the final matched study sample of 66 patients. The power to demonstrate the main effect of dronabinol over systemic analgesics is 80% using a 2-tailed alpha of 0.05. 

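### Length of stay is compared by a valid but unadjusted Wilcoxon test, giving up precision that covariates already used in the primary model could supply

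*Protocol article*

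**What the plan says.** Under 2.7. Statistics, the change in morphine equivalents is analyzed by ANCOVA "adjusted for age, gender, injury severity score", plus clinical characteristics that differ between the arms at p < 0.15. The same paragraph notes that polytrauma is allowed, and that any differences in injury pattern will be handled in the primary ANCOVA.

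The next paragraph fixes the secondary tests. Length of stay is listed with the other continuous secondary outcomes, which are "reported as median (IQR) and analyzed with a Wilcoxon rank-sum test". The categorical outcomes are "hospital disposition, hospital complications, and analgesic complications, reported as proportion (%) and analyzed with chi-square tests". No covariate is named for any of them.

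Two design features bear on this. Section 2.2 admits patients aged 18 to 65 with an injury to any body region. Section 2.4 stratifies randomization by habitual marijuana use only, so neither age nor injury severity is balanced by design.

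**The concern.** The article foresees chance imbalance in injury and corrects for it, but only in the primary analysis. Length of stay is an outcome that age and injury severity can reasonably be expected to influence. The Wilcoxon test takes no covariates, so variation that the trial has already measured is left in the error term.

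Two things follow if the covariates do predict length of stay. First, the comparison has less power than the same 122 patients could give. Second, if the realized arms differ in severity, the unadjusted result reflects that difference while the primary result in the same report is adjusted for it. What is at stake is the precision of one secondary comparison, and how it reads in a trial that happens to be unbalanced.

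**Working it through.** **The plan's own figure.** The article gives a sample size for the primary endpoint only: "The planned enrollment is 122 patients total randomized 1:1 across two study arms", 80% power, two-sided 0.05, "38% reduction in morphine equivalents with adjunctive dronabinol vs. an 8% reduction in morphine equivalents for systemic analgesics only". The pooled SD is stated as 58. Take the difference as 38 − 8 = 30 and the SD as 58, in the same unit.
- n per arm = 2 × (1.96 + 0.8416)² × (58/30)² = 58.7, so 59 per arm or 118 in total. A t-test version gives 60 per arm, 120 in total.
- Power at 61 per arm: 30 / (58 × √(2/61)) = 2.857, and 2.857 − 1.96 = 0.897, which gives 81.5% (80.9% by t-test).

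The stated 122 and 80% are therefore reproduced closely. No power or effect size is stated for length of stay, so the rest is conditional on assumptions.

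**Inputs for length of stay.** From the article: 61 per arm, and the general statement "Significance is set at an alpha value of 0.05", taken as two-sided. Assumed: R², the share of variance explained by the covariates, from 0.05 to 0.30, and a true shift of 0.5 SD, used only as an illustration.

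**Precision by formula.** For a linear model, the standard error shrinks by the factor √(1 − R²), and the equivalent sample size is 122/(1 − R²).
- R² 0.20: √0.80 = 0.894, so 11% narrower; 122/0.80 = 152.5.
- R² 0.30: √0.70 = 0.837, so 16% narrower; 122/0.70 = 174.

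**Power by simulation, rank method against rank method.** Skewed length of stay in whole days, 61 per arm, one standardized severity covariate, 6,000 runs per setting:

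| Assumed R² | Wilcoxon | Rank ANCOVA |
|---|---|---|
| 0.05 | 76% | 78% |
| 0.10 | 76% | 80% |
| 0.20 | 76% | 84% |
| 0.30 | 76% | 88% |

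Comparing two rank methods matters. Setting the Wilcoxon test against a linear model on normal data gives larger gaps (for example 76% against 86% at R² 0.20), but about 3 to 4 points of each come from the change of test, not from adjustment.

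**Type I error over all randomizations.** With no true effect and R² from 0.05 to 0.50, the Wilcoxon test rejected in 4.6% to 5.0% of runs. The chi-square test, simulated with a prognostic covariate, rejected in 4.8% to 5.4%. Both hold their level.

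**Behaviour given an imbalance.** The difference in mean severity, in SD units, has standard error √(2/61) = 0.181. A gap above 0.3 SD corresponds to |z| > 0.3/0.181 = 1.66, which has probability of about 10%. In those trials, with no true effect, the Wilcoxon test was falsely significant in roughly 11% (R² 0.20) to 17% (R² 0.30) of runs, against 4% to 6% for the adjusted test. These subsets hold only about 600 runs, so each figure carries a simulation error of a little over 1 point. The counterpart is that in the roughly 68% of trials with |z| below 1, the Wilcoxon error is below nominal: 4.2% at R² 0.05, falling to 1.6% at R² 0.50.

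**The case against.** The strongest reply is that nothing here is wrong. Wilcoxon and chi-square tests are valid after 1:1 randomization, and simple tests for secondary outcomes beside an adjusted primary model are ordinary practice. That stands in full. A reader might infer that severity imbalance biases these comparisons, or that section 2.7 contradicts itself. Neither is supported. Chance imbalance is already allowed for in the p-value, the overall error rate is about 5%, and the raised rate in unbalanced trials is offset by a lowered rate in the rest.

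A reader might also conclude that the chi-square tests for disposition and complications should be replaced. That does not follow either. No gain was calculated for those outcomes, logistic adjustment changes the target to a conditional odds ratio, and events may be sparse among 122 patients.

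The inputs are open to challenge too. The article gives no R² and never says that age or severity predicts length of stay; that is inferred from their place in the primary model. Its account of the preliminary cohort reports no differences in secondary outcomes, so a 0.5 SD shift has no support there. At 0.2 SD a normal approximation gives about 20% power unadjusted and 23% to 26% adjusted (R² 0.20 to 0.30), which is low either way. The simulation used one covariate where the proposal has three, though two more parameters cost little with 122 patients.

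Finally, supportive adjusted analyses are often left to the SAP, which is not shown. This carries less weight: the article names the test for length of stay, so the point concerns a stated choice and not an omission.

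**Conclusion.** The point holds as a minor matter of efficiency for one secondary outcome. The stated Wilcoxon test for length of stay is valid but gives up power if age, gender and injury severity score predict it: about 2 points at R² 0.05, 4 at 0.10, 8 at 0.20 and 12 at 0.30, for an assumed 0.5 SD shift. If the covariates explain little, or the true effect is small, the gain is slight. Sensitivity to a marked severity imbalance is real but conditional, arising in roughly one trial in ten. No stated figure, alpha level or primary conclusion is affected, and the tests for disposition and complications need no change on this ground.

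**What to change.** In section 2.7, make the length-of-stay comparison a pre-specified model with age, gender and injury severity score: either a rank ANCOVA or a proportional-odds model, with one of them chosen in advance. Keep the median (IQR) as description. Fixing the covariates beforehand matters because section 2.4 leaves the treatment team and statisticians unblinded, so adjustment added after an imbalance is seen would look data-driven.

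Keep the chi-square tests for disposition and complications. An adjusted logistic analysis there is at most an optional sensitivity analysis where event counts allow.

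The cost is a sentence of wording and a few lines of SAS, since the primary model already needs these covariates. The small downside is that the result is slightly less simple to report: a proportional-odds model gives an adjusted odds ratio, and a rank ANCOVA gives a test with no effect in days.

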### 2.8. Sample Size

The planned enrollment is 122 patients total randomized 1:1 across two study arms: dronabinol or no dronabinol (systemic analgesia only). The sample size is based on a 38% reduction in morphine equivalents with adjunctive dronabinol vs. an 8% reduction in morphine equivalents for systemic analgesics only, with a pooled standard deviation of 58. The analysis was performed using two sample mean tests with normal approximation and equal weights. These estimates were derived via bootstrapping of the final matched study sample of 66 patients. The power to demonstrate the main effect of dronabinol over systemic analgesics is 80% using a 2-tailed alpha of 0.05. 

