Recently published preliminary clinical research from our group examined the effect of adjunctive dronabinol for acute pain management among 66 trauma patients [10]. Cases demonstrated a significant reduction in opioid consumption (morphine equivalents) from baseline with adjunctive dronabinol (−79 mg, *p* < 0.001), while the change in opioid consumption for matched controls was unchanged from baseline (−9 mg, *p* = 0.63), resulting in a nine-fold greater reduction in opioid consumption for cases versus controls that was significantly different between pairs (difference: −70 mg, *p* = 0.02). There were no differences in secondary outcomes. These results suggest that adjunctive dronabinol used as part of a multimodal analgesia regimen may result in a marked reduction in opioid consumption

Two subset analyses of this matched cohort study provide mixed evidence that the opioid sparing effect of dronabinol may be greater in patients who are marijuana users. Among the subset of 19 cases who were marijuana users, opioid consumption was significantly reduced with adjunctive dronabinol (−97 mg, *p* < 0.001) versus no change in opioid consumption in 19 matched controls (1 mg, *p* = 0.70), with a difference between pairs that was significant: −108 mg, *p* = 0.01) [10]. However, when examining the subset of patients who received dronabinol, there were no differences in the change in opioid consumption for patients who were marijuana users (*n* = 21, −97 mg reduction with dronabinol) compared to non-marijuana users (*n* = 15, −64 mg reduction with dronabinol), *p* = 0.41 (unpublished). 

We are recruiting patients in a RCT to evaluate the efficacy of adjunctive dronabinol on opioid utilization for acute pain management. The primary trial objective is to evaluate the efficacy of adjunctive dronabinol versus control (systemic analgesics only, no dronabinol) for reduction in opioid consumption in adults with traumatic injury. Dronabinol is a licensed form of Δ^9^-THC. Dronabinol is not FDA approved for acute pain management; however, it has been in use at our level I trauma center system formulary without restriction since 2015. 

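### The 80% power is calculated for percent reduction in opioid use, but the primary analysis tests change in mg, so it is not a power for the primary endpoint

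*Protocol article*

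**What the plan says.** Section 2.8 sets the planning effect in relative terms: "The sample size is based on a 38% reduction in morphine equivalents with adjunctive dronabinol vs. an 8% reduction in morphine equivalents" in the control arm. The spread is given as "with a pooled standard deviation of 58", without a unit. The method is an unadjusted comparison of two means: "The analysis was performed using two sample mean tests with normal approximation and equal weights". The estimates come from a bootstrap of the 66-patient matched study, and power "is 80% using a 2-tailed alpha of 0.05". Enrolment follows: "The planned enrollment is 122 patients total randomized 1:1 across two study arms".

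Section 2.7 defines the primary endpoint as consumption after randomization minus consumption before it, and states the scale and model: "The change in morphine equivalents (mg) will be analyzed with an analysis of covariance (ANCOVA) model". The named covariates are age, gender and injury severity score, plus clinical characteristics that differ between the arms at p < 0.15.

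The Introduction reports the same 66-patient study in mg: a change of −79 mg in cases and −9 mg in matched controls (p = 0.63 for the control change), and a difference between pairs of −70 mg (p = 0.02).

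**The concern.** Percent change and change in mg are different variables, with different expected differences and different SDs. A power calculated for one does not carry over to the other unless the baseline distribution is known, and the article gives neither a mean baseline nor an SD of change in mg. The trial's only power statement therefore concerns a variable that its primary analysis does not test.

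The choice of scale also affects how robust the plan is. The Discussion accepts that opioid use may now be lower in both arms than in the 2017 data used for planning. If dronabinol's relative effect stayed the same, a lower baseline would leave a percent-scale calculation unchanged but shrink the difference in mg. A reader of section 2.8 cannot see that exposure.

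**Working it through.** **Inputs.** From section 2.8: 38% against 8%, SD 58, two-sided alpha 0.05, power 80%, 122 patients at 1:1 (61 per arm). From the Introduction: −79 mg and −9 mg, pair difference −70 mg, p = 0.02 between pairs, p = 0.63 for the control change, 66 patients (33 pairs if matched 1:1).

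**1. Reproduce the stated figure.** Take the difference as 38 − 8 = 30 and the SD as 58 in the same unit.

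- n per arm = 2 × (1.960 + 0.842)² × 58² / 30² = 58.7, so 59 per arm or 118 in total. The t-test version gives 60 per arm or 120 in total.
- Power at 61 per arm = Φ(30 / (58 × √(2/61)) − 1.960) = Φ(0.897) = 81.5%. The t-test version gives 80.9%.

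This agrees well enough with 122 patients and 80%.

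**2. Which unit do 30 and 58 share?** The only unit printed for the effect is percent. Two mg readings can be tested against the Introduction:

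- SD 58 mg with the preliminary 70 mg difference: n per arm = 2 × 7.849 × 58² / 70² = 10.8, so 11 per arm. That does not lead to 122.
- A difference of 30 mg with SD 58 mg fits numerically, but contradicts the 70 mg reported from the same 66 patients.

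Percentage points is thus the most plausible unit, although it is inferred.

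**3. What would power be in mg?** No SD of change in mg is given, so this step is an illustration. It assumes that the Introduction's figures are means tested by t-tests with 32 degrees of freedom.

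- Controls: p = 0.63 gives t = 0.486, SE = 9 / 0.486 = 18.5, SD = 18.5 × √33 ≈ 106 mg.
- Pair difference: p = 0.02 gives t = 2.449, SE = 70 / 2.449 = 28.6, SD of pair differences = 28.6 × √33 ≈ 164 mg.
- SD per arm = 164 / √(2(1 − r)), where r is the within-pair correlation: 116 mg at r = 0, 139 mg at r = 0.3, 164 mg at r = 0.5.

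For 61 per arm, power at 70 mg = Φ(70 / (SD × √(2/61)) − 1.960). The difference detectable with 80% power = 2.802 × √(2/61) × SD = 0.507 × SD.

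| Assumed SD (mg) | Power at 70 mg | Difference for 80% power |
|---|---|---|
| 106 | 95% | 54 mg |
| 116 | 91.5% | 59 mg |
| 139 | 79% | 71 mg |
| 164 | 65% | 83 mg |

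At 70 mg, power reaches 80% if the SD is at most 70 / 0.507 ≈ 138 mg.

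**The case against.** **The trial may be adequately powered anyway.** This stands. At the one mg effect that the documents give, 70 mg, power is close to or above 80% over most of the illustrative range. A reader might infer from the mismatch that the trial is underpowered, for instance by converting percentages to mg through an implied baseline. The documents do not support that. Equating the control figures (9 mg with 8%) implies a baseline of about 112 mg, at which a 38% reduction is 43 mg, not the reported 79 mg. Equating the case figures (79 mg with 38%) implies about 208 mg, at which an 8% reduction is 17 mg, not the reported 9 mg. No common baseline fits both arms, and the percentages may be means of individual percent changes, which cannot be converted this way.

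**The back-calculated SDs are fragile.** This also stands. The Introduction names no test. In its 19-pair subset the changes are −97 mg and +1 mg, yet the pair difference is −108 mg, where paired means would give −98 mg. The figures may be medians or adjusted estimates, in which case the SDs in the working have no basis.

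**An article condenses the full protocol.** This explains the missing unit, but not the conflict: both scales are printed, and they differ.

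**Covariate adjustment may add power.** It may, but section 2.8 assumes an unadjusted test, and adjustment does not turn an SD of percent change into an SD of change in mg.

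**The Discussion already discloses that consumption may have fallen.** It does, and it leaves the consequence for the treatment effect open. It does not say that the power was calculated on a different scale from the analysis.

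**Conclusion.** The point holds as a mismatch of scale. The stated 80% belongs to a comparison of percent reductions and is not a power for the mg-scale ANCOVA that is the primary analysis. It is not an arithmetic error, because the figure reproduces on its own scale (81.5%, or 80.9% by t-test).

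Power for the primary endpoint cannot be determined from the documents. The illustrative range at 70 mg is about 95% to 79% for SDs of 106 to 139 mg, and 65% at 164 mg. It rests on 1:1 matching into 33 pairs, t-tests on means, an assumed within-pair correlation, and a trial effect equal to the preliminary one. It shows that power in mg is uncertain, not that it is low. That 58 is in percentage points is an inference, but the conclusion needs only that section 2.8 plans on percent reductions while section 2.7 tests mg.

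**What to change.** Re-run the bootstrap of the 66-patient data for change in mg, over the windows used for the primary endpoint. In section 2.8, state the expected difference in mg, the SD of the change in mg with its unit, and the power and detectable difference for 61 per arm.

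The cost is a re-analysis of data already held and one rewritten paragraph; Trial Status records that this calculation has been amended once before. The restated power may be less favourable, and the sponsor would then have to decide whether 122 patients is still acceptable.

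Moving the primary analysis to a relative scale would also align the two sections, but it changes the question that the trial answers while an open-label trial is recruiting. That is a trade-off for the sponsor, not a required correction.

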### 2.9. Ethical Considerations

The study was approved from the Institutional Review Board for St. Anthony Hospital (Catholic Health Initiatives). There may be patients incurring cognitive impairment (due to head injury or acuity of illness). The study coordinator will discuss with the treating team and will directly assess the consenting capacity of the patient. The study nurse follows the current hospital protocol regarding the use of consent by a legally authorized representative. In these clinical situations where the patient’s representative initially consents, the patient will be "re-consented" when able to assure that they want to continue in the study. 

Safety outcomes will be reported to the head of the medical executive committee at an ongoing basis. If/when the rate and/or severity of the monitored safety events becomes unacceptable, the medical executive committee has procedures in place to protect research subjects.

An interim analysis will be performed when >50% (*n* = 62) of patients have been enrolled and discharged from the hospital to determine clinical equipoise. A stopping guideline of *p* < 0.001 will be used for the primary end point.

## 3. Discussion

This is the first randomized trial to investigate whether the addition of dronabinol is effective at reducing opioid consumption for acute pain management of traumatic injury. There are numerous strengths of this study. This clinical trial improves upon our previously published matched cohort study and removes many of the limitations of that study: patients will now be matched by self-reported marijuana use; the pre-treatment period for the controls will be identical to cases rather than being estimated based on the median time from admission to first administration of dronabinol among cases; we will know why controls were not prescribed dronabinol; there are complications and adverse effects that are associated with both systemic analgesics and dronabinol, which will be recorded and analyzed in this trial by treatment arm and by severity. Additional strengths of this study are that it is investigator-initiated and independent from pharmaceutical or other industry interests, and the findings (whether positive or negative) will be submitted to a peer reviewed scientific journal for publication.

Another benefit of this study is the stratified randomization by chronic marijuana usage. Earlier work by the study investigators suggests that pre-injury marijuana use results in increased consumption of opioid analgesics and greater self-reported pain following traumatic injury compared to trauma patients who are marijuana naïve [12]. If the randomized trial demonstrates a greater treatment effect in the subset of chronic marijuana users, this will have wide-ranging clinical implications for acute pain management, because trauma patients have a high prevalence of marijuana use and other substance abuse issues, reported in 40–50% of patients [13,14] that appears to be increasing over time [15]. Thus, if marijuana use significantly affects acute pain management then chronic marijuana users will merit special consideration during acute pain management. 

While there are now 11 states that have legalized recreational marijuana, we believe Colorado is uniquely able to study this issue because of the high utilization in our state. Colorado was the first state to legalize and commercialize recreational marijuana, with retail shops opening on January 1^st^, 2014. A recent study identified that commercialization of recreational marijuana in Colorado was associated with an increased use of marijuana or an increased risk of traumatic injury while using marijuana [15]. 

Opioids are established and effective analgesics for managing pain in the traumatic and critical care setting due to their proven efficacy in treating moderate to severe acute pain [16]. The Center for Disease Control and Prevention (CDC) estimates that approximately 130 Americans are dying each day from opioid overdose, resulting in an opioid epidemic. We believe the use of dronabinol as a tool in the clinician’s tool kit to decrease reliance on opioids is an appealing option. Some possible benefits of this study include better pain control and a lower need for opiates for participants. Use of dronabinol to reduce or maintain the opioid regimen, rather than increasing narcotic dosages to detrimentally high levels, may also reduce the negative effects of opioids on vascular neurologic response and respiratory depression.

One of the primary limitations of this trial is that the study is open label. Patients are still prospectively randomized to active treatment vs. control and all assessments are standard and routinely collected by the assessors (ICU and general ward nursing staff), including pain scores and analgesia administration. However, we are unable to blind patients because there are no orally administered placebo pills that are on hospital formulary to be used for this study (unavoidable blinding). We did not blind clinicians because the dosing of dronabinol may need to be modified and is allowed within the range of 5 mg to 30 mg daily in divided doses. Although a blinded study would be preferred to reduce knowledge bias, the study design is compatible with real-world situations and increases the external validity of the study. 

Additional limitations are as follows. First, our preliminary study was conducted in 2017, around the peak of the opioid epidemic [17,18]. Since that time, there have been enterprise-wide initiatives to use alternatives to opioids [19,20], which could impact our enrollment criteria. However, our study has potentially greater implications in the current setting where opioid alternatives are sought. Second, and related, the data used to power the RCT were recorded in 2017, and it is possible that opioid consumption will be less in both groups (dronabinol and control), but whether this translates to a different treatment effect with dronabinol remains to be seen. Third, marijuana use is based on self-reporting because admission urine toxicology testing is only utilized in about 50% of patients, with a bias towards screening younger patients. Unlike blood alcohol tests, urine toxicology testing seldom results in a change in care and thus are not routinely ordered following traumatic injury. We will not be requiring a change in practice for ordering urine toxicology testing as part of our study. However, our unpublished research demonstrates the percent agreement between urine toxicology findings and patient self-report is 81% for cannabis. The negative predictive value of 95% demonstrates that a negative self-report correctly identifies 95% of patients who test negative for cannabis, while the specificity provides an 85% chance that a patient will not test positive for cannabis if the patient denies use. Fourth, the results of this study are only be applicable to dronabinol and not to other cannabinoids, such as the recently trending cannabidiol (CBD). Finally, the study is currently approved as a single-center RCT, which limits its generalizability. The authors are amenable to adding additional sites which use dronabinol on formulary without restrictions. 

There are two additional risks to the patient that need to be mentioned. First, this study involves an experimental (investigational) drug that has not been approved by the U.S. Food and Drug Administration (FDA) for the specific indication of acute pain management. Dronabinol is only FDA approved for loss of appetite due to HIV and chemotherapy-induced nausea and vomiting. This study is not intended to result in an FDA Investigational New Drug Application. Second, dronabinol is a synthetic version of THC. There is a risk that the study medication will result in a positive urine drug screen test for cannabis for two weeks or more in patients who are not a current user of marijuana products. In most cases, if an employee has a recent prescription for dronabinol, that is sufficient to report the result to the employer as a negative. 

